### Control Group

The control group will continue to work as normal with no changes in their routine or environment. They will complete the same measurements as the intervention group.

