##### Productivity

Work productivity will be assessed using measures of absenteeism, presenteeism, and ecological momentary assessment (EMA) at baseline and during week eight of the study. Absenteeism will be measured using self-report at baseline and at the end of the eighth week. Three questions to assess unsanctioned absences will be used from a previous study (45). This includes the number of days off work in the last 2 weeks for sickness (colds, flu, etc.), the number of days off work for mental health reasons (stress, burnout, etc.), and the number of days excused work (e.g., compassionate leave, educational leave, parental leave). Self-reported absenteeism will be calculated by summing the number of days reported across all three questions. Presenteeism will be measured using the 8-item Work Limitations Questionnaire (WLQ), which is a short version of the original 25-item WLQ (46). This version of the WLQ is a reliable and valid alternative to the longer questionnaire (47). The WLQ requires participants to self-report their level of difficulty (or ability) to perform eight specific job demands in the last 2 weeks, with answers grouped into four work limitation scales on time management, physical, mental, and output demands.

The final measure of productivity is EMA, which has been used previously in a variety of different contexts to measure physical activity and sedentary behavior (48–50). Prompt software will be installed on participant's smartphones to deliver the EMA. Prompts to complete the EMA will occur at random, four times each week day between 9 am to 5 pm (51). In total, participants will be requested to respond to and complete a maximum of 12 EMA surveys in a week. Once a participant has completed 12 surveys, the prompt software will no longer prompt that participant to respond (51). The questionnaire includes items about posture, musculoskeletal issues, task being performed, social interactions, mood, and perception of engagement and productivity (Table 5), typically taking <1 min to complete each time.

**Table 5 T5:** Ecological momentary assessment productivity questions.

**Survey question**	**Responses**
What posture are you in?	Sitting/Standing/Walking
Are you experiencing musculoskeletal pain right now?	Yes/No
What are you currently doing?	In a meeting/Working at my desk/Working away from my desk/Eating/In transit/On a break/Other

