### Statistical Analysis

All statistical analyses will be performed using SPSS (IBM Corp, Armonk, New York, USA). Data will be assessed for normality using the Shapiro-Wilk test owing to the relatively small sample size. Linear mixed models will be used with arm and time as fixed effects, participant ID and cluster ID as random effects, and the baseline value of each variable as a covariate. An additional linear mixed model will be used to compare the effect of standing vs. sitting posture for the EMA variables at follow-up with posture and arm as fixed effects, participant ID and cluster ID as random effects, and the baseline value of each variable as a covariate. The Sidak *post-hoc* adjustment will be used to adjust for multiple comparisons in all models. Adjustments for missing data will be made using the estimated marginal means procedure of the linear mixed models. If there was a large number of non-normally distributed variables, the bias-corrected and accelerated (BCa) bootstrap method will be used to produce unbiased estimates of the confidence limits for all data (62). Data will be presented as mean and 95% confidence intervals of the bootstrapping procedure. The level of statistical significance will be *p* ≤ 0.05 for two-tailed tests. Magnitude of effects will be reported as Hedges' *g*, which is a corrected effect size based on Cohen's *d* that is suitable for use in small sample sizes of 20 or less per group to produce an unbiased estimate of the population effect size (63). The magnitude of the effect sizes will be considered to be small if they are ≥ 0.2, moderate if ≥ 0.6, and large if ≥ 1.2, using the scale proposed by Hopkins et al. (64). Adherence to the intervention will be assessed using the Wilcoxon signed rank test to compare baseline and follow-up classifications. The standardized test statistic of the Wilcoxon test will be converted to an effect statistic by dividing it by the square root of N (65), which can then be interpreted as *r* using the scales of Cohen (66) and Hopkins et al. (64).

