## Discussion

This pilot cluster-randomized controlled trial will evaluate the efficacy of a tailored workplace intervention for reducing and breaking up sitting, productivity, wellbeing and cardiometabolic risk biomarkers. The multi-component intervention protocol was designed using a participatory approach informed by the BCW and identification of intervention functions, policy categories and BCTs using the APEASE criteria to enhance the intervention's adherence and effectiveness. In addition to employing this systematic and evidence-based process for developing the intervention, further strengths of this study include the cluster-randomized design to minimize contamination between groups that are located within the same organization. The study will also be conducted within an ecologically valid office environment, thus enhancing its real-world application. Ecological momentary assessment will be used to assess temporal effects of the intervention on productivity during specific postures and work activities; this may provide important evidence to encourage changes in workplace policy and practice. Potential limitations include sample representativeness of the general office worker population as the study is being conducted only within two organizations. It will also not be possible to determine the effects of each individual strategy used as part of the intervention, which could help in determining their suitability for inclusion in occupational health promotion programmes. Furthermore, physical activity levels prior to taking blood samples will not be standardized. This may be a limitation as there is the potential for carryover effects of prior exercise on glucose and lipid levels.

In conclusion, this study will provide important evidence regarding the efficacy of a systematically developed tailored workplace intervention. This will include evaluating the effects of the intervention on a range of health and work-related outcomes, including an ecological momentary assessment of productivity that has been seldom employed in office workplace studies; this may be key in promoting the adoption and implementation of such interventions in workplace practice and policies. The findings of this study can be used to inform a future fully powered RCT to determine the effectiveness of this multi-component intervention for reducing sitting and improving health in office workers.

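### The EMA posture model omits the activity recorded at the same prompt, so its standing-versus-sitting estimate is open to confounding by task

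*Protocol article*

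**What the plan says.** All references are to the protocol article.

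- **Statistical Analysis.** After the main arm-and-time models, an additional linear mixed model will "compare the effect of standing vs. sitting posture for the EMA variables at follow-up with posture and arm as fixed effects". The random effects are for person and office cluster, and each variable's value at baseline enters as a covariate. No activity term and no posture-by-arm term is named.
- **Productivity, Table 5.** Each EMA survey asks for posture (sitting, standing or walking) and, in the same sitting, for current activity: "In a meeting/Working at my desk/Working away from my desk/Eating/In transit/On a break/Other". Ratings such as productive, engaged and stressed run from 1 to 10. Prompts fall at random between 9 am and 5 pm on weekdays, up to 12 completed surveys a week.
- **Intervention Development, Content and Delivery** puts a height-adjustable workstation at each intervention participant's desk. Under **Control Group**: "The control group will continue to work as normal with no changes in their routine or environment".
- **Discussion.** EMA will be used to "assess temporal effects of the intervention on productivity during specific postures and work activities".

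**The concern.** The model is described as estimating an effect of posture, but posture at a prompt is not randomised. It goes with whatever the person is doing. If standing moments contain a different mix of desk work, meetings, meals and breaks than sitting moments, and the ratings differ by activity, the posture coefficient absorbs part of the activity difference. Arm, baseline value and a participant intercept are constant across one person's follow-up prompts, so they cannot remove confounding that varies from prompt to prompt.

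Two features sharpen this. First, the trial gives only the intervention arm a means of standing while doing desk work. The link between posture and task therefore plausibly differs by arm, yet one common posture coefficient is fitted. Second, with a random intercept and posture entered as it stands, that coefficient blends two contrasts: change within a person, and differences between people who stand a lot and people who do not.

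The Introduction says managers may resist these interventions if productivity suffers, and the Discussion says the EMA results may help adoption. An apparent harm or benefit of standing that came from task mix would mislead those readers. The activity variable is already collected, and the stated aim of reporting by work activity is not served by any stated model.

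**Working it through.** The article gives no figure for this model, so there is none to reproduce. The check asks how large the distortion could be, and when it is nil.

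**Inputs from the article.** Two groups of 18 (Sample Size), at most 12 surveys per person in the week (Productivity), two-sided 0.05 (Statistical Analysis). Maximum responses: 36 x 12 = 432.

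**Assumed inputs (not in the article).** True standing effect 0. Ratings are 0.5, 1 or 2 points higher during desk work. Desk-work share of sitting responses 0.9. Desk-work share of standing responses 0.8 in the intervention arm and 0.2 or 0.5 in controls. Standing share of responses 15% in controls and 35% in the intervention arm. Residual SD 1.5.

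**Step 1, bias within one arm.** Bias = task effect x [P(desk | standing) - P(desk | sitting)]. With a 1-point task effect:

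- controls at 0.2: 1 x (0.2 - 0.9) = -0.7
- controls at 0.5: 1 x (0.5 - 0.9) = -0.4
- intervention at 0.8: 1 x (0.8 - 0.9) = -0.1
- either arm at 0.9: 1 x (0.9 - 0.9) = 0

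The sign is not fixed. If 0.9 of standing and 0.8 of sitting responses were desk work, the bias would be 1 x (0.9 - 0.8) = +0.1.

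**Step 2, the common coefficient.** With equal arms, a within-person estimate weights each arm by the variance of posture: 0.15 x 0.85 = 0.1275 for controls and 0.35 x 0.65 = 0.2275 for intervention. The weights are 0.1275/0.355 = 0.36 and 0.64. Pooled bias at a 1-point task effect:

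- controls at 0.2: 0.36 x (-0.7) + 0.64 x (-0.1) = -0.32
- controls at 0.5: 0.36 x (-0.4) + 0.64 x (-0.1) = -0.21

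**Step 3, simulation.** 4000 runs per scenario, 36 people x 12 surveys, participant intercepts removed by centring each person's data.

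| Task effect (points) | P(desk given standing), control / intervention | Standing estimate without activity | False-positive rate |
|---|---|---|---|
| 0.5 | 0.2 / 0.8 | -0.16 | 14% |
| 1 | 0.2 / 0.8 | -0.32 | 41% |
| 2 | 0.2 / 0.8 | -0.63 | 89% |
| 0.5 | 0.5 / 0.8 | -0.10 | 9% |
| 1 | 0.5 / 0.8 | -0.21 | 21% |
| 2 | 0.5 / 0.8 | -0.41 | 55% |
| 0.5, 1 or 2 | 0.9 / 0.9 | about 0 | about 5% |

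With activity in the model, the estimate was about 0 and the false-positive rate about 5% in every row. The 1-point rows agree with Step 2.

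**Limits of the check.** Activity was reduced to desk work or not. Walking responses, the cluster effect and the baseline covariate were left out. The simulation isolates prompt-level confounding and does not size the blending of within-person and between-person contrasts.

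**Step 4, desk-work responses only.** Controls give 18 x 12 = 216 responses. At 15% standing and 0.2 of those at desk work, 216 x 0.15 x 0.2 = 6.5 are standing desk-work responses. At 0.5 the number is 16.2. In the intervention arm it is 216 x 0.35 x 0.8 = 60.5.

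**The case against.** The strongest reply is that the article reports nothing about what people do while standing, so the size of any bias is whatever one assumes. That stands. The negative figures follow from the assumed direction, and the bias is zero if task is unrelated to posture or to the rating. People may also sit for meals and breaks, which would shrink or reverse it. Walking is a separate response in Table 5, so some transit lies outside the standing-versus-sitting contrast. The baseline covariate absorbs part of the stable differences between people. The model is labelled additional, and the arm-and-time models carry the randomised comparison. All of this limits the weight of the point. None of it removes prompt-level confounding or explains why a variable collected for the purpose goes unused.

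A reader might infer more than the article supports:

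- **That any standing effect is really a task effect, or that controls mostly stand away from desk work.** The article shows only who is given a workstation. It has no data on activity by posture and does not say whether any control already had a sit-stand desk.
- **That the limit of 12 completed surveys biases the contrast.** With four prompts a day, a full responder finishes in 12/4 = 3 days and a 60% responder in 12/2.4 = 5 days, so the weekdays sampled depend on compliance. Nothing in the article links weekday to the relation between posture and ratings, so no change to the prompt schedule is proposed.
- **That the posture model is presented as proof that standing does not harm productivity.** The Discussion speaks more cautiously, of effects of the intervention and of evidence that may help adoption.

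**Conclusion.** The point holds as a weakness in a written specification: the standing-versus-sitting estimate is open to confounding by an activity variable that is recorded at the same prompt but not used, plausibly more so in controls. The stated model also falls short of the Discussion's aim of examining productivity by work activity. Its actual size and direction are unknown. Under the assumed inputs the pooled spurious difference ranged from 0 to -0.63 points, with false-positive rates from about 5% to 89%; other inputs could give a positive difference. These figures show what the model would allow and do not predict the trial's result. The matter is confined to a secondary analysis in a pilot. Workplace sitting time, the primary outcome, is not affected. Because the remedy needs no new data, it is worth making before the EMA data are analysed.

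**What to change.** Keep all sitting and standing responses in the main posture model and change its terms:

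1. Add recorded activity as a fixed effect.
2. Add a posture-by-arm term, and show the posture estimate by arm.
3. Enter posture as the participant's mean plus the deviation from that mean, and report the deviation (within-person) coefficient as the result.
4. Repeat the model on desk-work responses as a sensitivity analysis only, stating how many control responses are standing; Step 4 of the working suggests there may be very few.

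Even then the estimate is an observational association within the trial, and should be described so, because tasks can differ within one activity category.

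The cost is a few degrees of freedom: six for the seven activity options, one for the interaction and one for the participant mean, out of at most 432 responses. Intervals will be slightly wider. No extra data collection is needed.

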There is a growing body of evidence that suggests height-adjustable workstations (i.e., a workstation that permits the user to interchangeably work in a seated or standing posture) could be effective for decreasing sitting in the workplace (13). When height-adjustable workstations are provided as part of multi-component interventions that also include strategies such as education, manager support, standing meetings, self-monitoring and social support, workplace sitting has been significantly reduced by 45 to 83 min/work shift after 12 months (14, 15). Although these interventions appear promising, management of organizations might be reluctant to implement them if productivity is negatively affected (16). With respect to productivity concerns, a systematic review reported that productivity is likely to be unaffected by using a height-adjustable workstation (17). There are also limited studies that have reported taking employee's perceptions and experiences into account when developing interventions to reduce workplace sitting (18), which may limit intervention adherence and effectiveness. By involving the target audience in the development of interventions, this will help to ensure their needs are met and enhance their adherence and engagement (19). The Behavior Change Wheel (BCW) (20, 21) has been recommended for guiding the systematic process of developing an intervention using a framework that takes into account the needs of the target audience. To the author's knowledge, only one previous office workplace intervention has been developed using the BCW (18); the SMArT Work intervention in National Health Service employees led to significant reductions in sitting at work and improvements in job performance, work engagement, occupational fatigue, sickness presenteeism, anxiety and quality of life over 12 months (15). Further research is required in other occupational groups to strengthen the evidence base for incorporating a focus on reducing and breaking up sitting in workplace policy and practice. Demonstrating the effectiveness of such interventions for improving work-related outcomes, such as worker productivity, will be important for encouraging the adoption of such changes in policy and practice. The use of ecological momentary assessment (EMA) facilitated through smartphone technology provides the opportunity to collect simultaneous time-stamped data with limited recall bias to elucidate on the temporal effects of posture and activities on work performance throughout the workday (22, 23). However, the effects of workplace sitting interventions on EMA measures of work-related outcomes is limited.

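### The EMA standing-versus-sitting coefficient blends a within-person contrast with a residual between-person one, and leaves time of day and current task unadjusted

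*Protocol article*

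**What the plan says.** The Statistical Analysis section of the protocol article specifies an extra linear mixed model to "compare the effect of standing vs. sitting posture for the EMA variables at follow-up with posture and arm as fixed effects". The same sentence adds "participant ID and cluster ID as random effects, and the baseline value of each variable as a covariate". Posture is a single term. The model has no person-mean or person-centred posture, no hour of day and no current activity, and no other section adds them.

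The Productivity section describes the data. "Prompts to complete the EMA will occur at random, four times each week day between 9 am to 5 pm", and "participants will be requested to respond to and complete a maximum of 12 EMA surveys in a week". Each survey covers "items about posture, musculoskeletal issues, task being performed, social interactions, mood, and perception of engagement and productivity", so posture and current task are recorded together (Table 5). The Introduction presents smartphone EMA as a way to "collect simultaneous time-stamped data with limited recall bias to elucidate on the temporal effects of posture and activities on work performance throughout the workday". The Discussion says: "Ecological momentary assessment will be used to assess temporal effects of the intervention on productivity during specific postures and work activities".

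**The concern.** Arm is randomised, but posture at a prompt is not. People differ in how often they stand, and a participant's posture may depend on the hour and on the work in hand. With raw posture and a random intercept, the coefficient is a weighted mix of two contrasts:

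- how one person's rating differs between standing and sitting prompts;
- how people who stand often differ from people who seldom do.

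The random intercept assumes that a person's level is unrelated to the tendency to stand. Where that fails, part of the second contrast enters the result. The baseline value reduces that part, but it comes from at most 12 surveys and a person's level can shift over eight weeks.

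Hour and task raise a separate problem. They vary within a person, so neither the random intercept nor the baseline value can absorb them. If ratings drift over the day and standing is commoner at some hours, the drift is attributed to standing. Task works in the same way.

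At stake is how one secondary EMA result is read: the plan would label an observational contrast an effect.

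**Working it through.** **Inputs from the article.** Model terms, prompt schedule, a maximum of 12 surveys per week, about eight clusters, and two groups of 18 completers (36 people). The recruitment target of 44 is 36 × 1.2 = 43.2, rounded up; 36 / 0.8 would give 45. The point does not turn on this, and only the 36 is used. The article states no size for the posture contrast, so there is no figure to reproduce.

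**Assumed inputs.** ICC (the person share of rating variance), posture split, correlation of person level with standing, and hour slopes. The article gives none of these, so ranges are shown.

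**Step 1: weight of the between-person contrast.** Let m be the prompts answered per person and b the between-person share of posture variance. In a random-intercept model:

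ψ = (1 − ICC) / (1 − ICC + m·ICC); weight = ψb / [(1 − b) + ψb]

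| m | ICC | b | ψ | Weight |
|---|---|---|---|---|
| 12 | 0.6 | 0.1 | 0.4/7.6 = 0.053 | 0.6% |
| 12 | 0.4 | 0.3 | 0.6/5.4 = 0.111 | 4.5% |
| 12 | 0.2 | 0.5 | 0.8/3.2 = 0.25 | 20% |
| 4 | 0.6 | 0.1 | 0.4/2.8 = 0.143 | 1.6% |
| 2 | 0.2 | 0.5 | 0.8/1.2 = 0.667 | 40% |

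The slope is mostly a within-person contrast at 12 prompts, and less so when few are answered. The bias is this weight times whatever between-person difference remains after baseline adjustment.

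**Step 2: person and hour confounding, true effect 0.** 36 people in eight clusters, 1,500 replicates, variances treated as known, no separate cluster term in the fit. Person SD 1.2, change SD 0.6, cluster SD 0.3, prompt SD 1.5. Log-odds of standing rise by 1 per person SD (person rows) and fall by 0.15 per hour (hour rows). Mean estimated standing effect, in points (Monte Carlo SE at most 0.009):

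| Confounding | No person term | As planned | + person mean | + person mean and hour |
|---|---|---|---|---|
| Person, 12 prompts | 0.97 | 0.045 | 0.011 | 0.010 |
| Person, 6 prompts | 0.982 | 0.070 | 0.016 | 0.017 |
| Hour, rating −0.05 per hour | 0.041 | 0.034 | 0.034 | −0.006 |
| Hour, rating −0.15 per hour | 0.126 | 0.123 | 0.123 | 0.005 |
| Person and hour (−0.15) | 1.058 | 0.160 | 0.127 | 0.009 |

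The planned model lets through 0.045/0.97, about 5%, of the person-level bias. Hour bias passes almost whole (0.123 of 0.126), is untouched by the person mean, and goes only when hour is added. A smaller run with fully fitted mixed models (80 replicates, many convergence warnings) gave the same pattern with a larger residue, about 0.14 against 1.04.

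**Step 3: person part with correlation 0.3, 0.5 and 0.7 between level and tendency to stand.**

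- 6 prompts (300 trials): bias 0.044, 0.113, 0.135; false positives 7–9%.
- 10 prompts (300 trials): bias 0.039, 0.069, 0.086; false positives 4–6%. Simulation error on these rates is √(0.05 × 0.95 / 300), about 1.3 percentage points.
- 12 prompts (2,000 replicates): bias 0.03, 0.05, 0.07; false positives 5.8%, 6.0%, 7.5%.

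A further simulation, also with assumed inputs, gave bias of 0.04–0.07 at 12 prompts and 0.09–0.18 at 4, with false positives of about 5–9%. Person-mean centring removed the bias and raised the SD of the estimate by 4–11%.

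Task was not simulated. The reasoning for hour carries over because task also changes within a person.

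**The case against.** The strongest reply is that the plan already protects itself. The participant random effect and the baseline covariate stand in the same sentence as the posture term, and they remove about 95% of the person-level bias in Step 2. With 10 prompts answered, false positives of 4–6% cannot be told from 5%. Centring also costs precision: at 12 prompts the root mean squared error was 0.178, 0.183 and 0.191 as planned against 0.181, 0.181 and 0.180 centred, so overall accuracy is close to a tie. The hour result rests wholly on assumed slopes, and the documents give neither their size nor their direction. This is an additional model for secondary items in a pilot, and an article may leave refinements to a fuller plan.

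Most of this stands and limits the size of the point. It does not remove it. The article states the model's terms outright, so this is not a detail left open. Twelve surveys is a maximum, and the residue grows as fewer are answered or as more people report only one posture. Nothing in the model addresses hour or task.

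A reader might infer that the model would report a benefit of standing where none exists. The figures do not support that: they show a small shift and a mild rise in false positives. A reader might also take the Discussion to rest policy change on this coefficient. That sentence concerns the intervention's effects during particular postures and activities, and says only that they may provide evidence for policy.

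**Conclusion.** The point holds in a limited form. The posture coefficient is a blend: mainly within-person, with a residual between-person share. Under the assumed inputs the person part is about 0.04 to 0.18 points on the 1–10 scale, running from 12 answered prompts down to 4 (one run gave 0.03 at 12 prompts with the weakest correlation). False positives are about 5–9%. Hour confounding of 0.03 to 0.12 points passes through under the assumed slopes, and its real size and sign are unknown. Task is unquantified. The correlation, ICC, posture split and slopes are all assumptions, and other values would change these sizes.

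The primary outcome (workplace sitting by activPAL) and the comparison between arms are not affected. The change is worth making because it brings the model closer to the stated interest in "temporal effects of posture and activities on work performance throughout the workday" using data already planned.

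**What to change.** Amend the sentence on the additional EMA model as follows:

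- Enter posture as two terms: the participant's mean share of standing, taken over the sitting and standing prompts in the model, and the prompt-level deviation from that mean. Report the deviation coefficient as the posture result.
- Add hour of day, from the prompt's time stamp, and current task, from the EMA survey, as covariates.
- Describe the result as an association between posture and rating, not an effect of posture.

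It would help to report how many participants gave only one posture, because they contribute nothing to the deviation term.

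No new data are needed. Centring raises the SD of the estimate by about 4–11%, so the change is cheap but not free. The precision cost of the hour and task terms was not assessed. Even with these terms posture remains self-selected, so the wording change is needed whichever covariates are used.

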### Sample Size

There is no standard procedure for determining the sample size for pilot studies as their main purpose is to obtain an estimate of the standard deviation that could be used to determine the likely effect size to inform a full trial (25). Thus, the proposed study will recruit a total of 44 participants in two groups of 18 allowing for an attrition rate of 20%. This is in line with sample size recommendations for pilot studies (26) and that used in a previous related pilot study of a workplace intervention to reduce sitting (27).

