### Randomization

To minimize contamination between groups in open plan offices, a cluster randomization approach will be used with offices being the unit of randomization i.e., randomization into either the intervention or control group will be assigned on an office basis (28). The number of clusters is projected to be approximately eight with an average cluster size of six (29). Randomization will be achieved by assigning a cluster ID to each office and clusters then being allocated to intervention or control group using an online randomization tool (https://www.randomlists.com/team-generator) by an independent researcher (30). Randomization will take place before the collection of baseline measurements and group allocation will not be disclosed to participants until the completion of baseline assessment (28).

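### With about eight randomised offices, the conditional switch to BCa bootstrap intervals for every outcome does not give the unbiased 95% limits that the plan claims

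*Protocol article*

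**What the plan says.** All references are to the protocol article.

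- **Randomization:** "a cluster randomization approach will be used with offices being the unit of randomization". On numbers: "The number of clusters is projected to be approximately eight with an average cluster size of six".
- **Statistical Analysis, model:** "Linear mixed models will be used with arm and time as fixed effects, participant ID and cluster ID as random effects", with the baseline value as a covariate. Significance is set at p "≤ 0.05 for two-tailed tests".
- **Statistical Analysis, bootstrap:** normality of the data is checked with the Shapiro-Wilk test. The switch follows from the condition "If there was a large number of non-normally distributed variables", and then "the bias-corrected and accelerated (BCa) bootstrap method will be used to produce unbiased estimates of the confidence limits for all data". The next sentence says that means and 95% bootstrap intervals will be presented.
- **Statistical Analysis, multiplicity:** a Sidak "adjustment will be used to adjust for multiple comparisons in all models".

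**The concern.** A bootstrap interval takes its width from the spread of resampled estimates. In a cluster trial the information about the arm effect sits largely in the randomised offices, so either choice of resampling unit runs into trouble here:

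- **Resampling participants** treats people in one office as independent, and so leaves out the between-office variation that office randomisation brings into the arm comparison.
- **Resampling offices** respects the design but has about four units per arm to work with. The bootstrap then understates the standard error and behaves as if it used normal rather than t quantiles. BCa corrects for bias and skewness in the bootstrap distribution. It does not correct for having so few units.

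The trigger adds a second problem. The assumption of a linear mixed model concerns residuals and random effects, not the raw variables. The rule also acts on all outcomes together: if many secondary variables look non-normal, the primary outcome (percentage of work time spent sitting) is switched to the bootstrap even if its own residuals are unremarkable.

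The article speaks of efficacy, sets a significance level, and says that the findings can inform a fully powered trial. Intervals that are too short would overstate how much the pilot has learned.

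**Working it through.** **Inputs from the article.** About 8 offices; two arms; nominal 95% intervals. The target of 44 participants reproduces from two groups of 18: 36 × 1.2 = 43.2, rounded up to 44 (dividing by 0.8 would give 45). Participants per office: 44/8 = 5.5 recruited, or 36/8 = 4.5 after attrition.

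**Assumptions, not in the article.** Equal split (4 offices per arm), 5 participants per office, ICC 0 to 0.20, normal or log-normal individual errors.

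**Step 1: approximate calculation, normal errors.**

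*Offices resampled.* With k = 4 offices per arm, the bootstrap standard error is √((k−1)/k) = √0.75 = 0.866 times the usual one. With normal quantiles the half-width is 1.96 × 0.866 = 1.697 usual standard errors, whereas the t quantile with 6 df is 2.447. Coverage is P(|t₆| < 1.697) = 85.9%.

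*Participants resampled.* With n = 20 per arm, the design effect is D = 1 + (5−1) × ICC, and the expected within-arm sample variance is (20−D)/19 of the true total. The half-width in true standard errors is 1.96 × √(19/20) × √[((20−D)/19)/D]:

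- ICC 0: D = 1.0, half-width 1.910, normal coverage 94.4%
- ICC 0.05: D = 1.2, half-width 1.735, coverage 91.7%
- ICC 0.10: D = 1.4, half-width 1.597, coverage 89.0%
- ICC 0.20: D = 1.8, half-width 1.394, coverage 83.7%

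**Step 2: simulation of BCa itself.** 8,000 trials per scenario, 999 resamples, difference in arm means, no true effect. The Monte Carlo standard error is √(p(1−p)/8000), or 0.2 to 0.5 points.

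| Errors | ICC | BCa, participants | BCa, offices | Office-level t, 6 df |
|---|---|---|---|---|
| Normal | 0 | 93.3% | 85.2% | 94.9% |
| Normal | 0.01 | 93.1% | 86.0% | 95.4% |
| Normal | 0.05 | 91.1% | 85.7% | 95.3% |
| Normal | 0.10 | 88.0% | 84.9% | 94.7% |
| Normal | 0.20 | 82.2% | 84.8% | 94.4% |
| Log-normal | 0 | 86.2% | 82.9% | 95.8% |
| Log-normal | 0.01 | 86.1% | 83.5% | 96.0% |
| Log-normal | 0.05 | 82.6% | 84.2% | 95.7% |
| Log-normal | 0.10 | 79.8% | 84.6% | 95.6% |
| Log-normal | 0.20 | 74.2% | 85.0% | 95.2% |

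A separate run with 1,500 trials per scenario gave about 81–94% (participants, normal), 75–88% (participants, log-normal), 84–86% (offices) and 95–96% (office-level t). The two runs agree apart from simulation error, and the normal-error rows match Step 1 to within about 1.5 points.

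**Step 3: is the number of offices the cause?** Four offices per arm allow only C(7,4) = 35 distinct resamples per arm. With 20 offices per arm and normal errors, office resampling covers 93.1% to 93.5% (ICC 0 to 0.10). Few offices therefore explain most of that shortfall.

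**Step 4: Sidak.** The adjusted level is 1 − (1 − 0.05)^(1/m). Arm, time and posture (standing vs. sitting) each have two levels and no interaction is listed, so m = 1 and the level stays at 0.05.

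**The case against.** **The bootstrap is conditional.** A reader might infer that every published interval will be too narrow. The text does not support that: BCa applies only if many variables are non-normal. The following sentence, on presenting bootstrap intervals, does not repeat the condition, but it reads most naturally as part of the same rule. This stands, and it limits the point to the case where the switch is made.

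**The shortfall can be small.** At ICC 0 with normal errors, resampling participants covers about 93%. This also stands. But the switch is meant for non-normal data, and with log-normal errors coverage is 86% at best.

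**The resampling unit may be set elsewhere.** It may, and its absence from an article is not counted here. Much of the participant-level loss comes from ignoring offices rather than from BCa: an ordinary person-level t interval on the same layout covers 95.0%, 92.7%, 90.1% and 85.1% at ICC 0, 0.05, 0.10 and 0.20. Naming offices as the unit would not rescue the claim, because office resampling still covers only 83% to 86%.

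**The simulation is not the full model.** True. It has no baseline covariate, unequal offices or repeated measures. With balanced offices and no covariate, however, the mixed-model arm estimate is the difference in arm means, so the mechanism carries over even if the exact percentages shift.

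**It is a pilot.** This lowers the stakes. It does not make the stated property true.

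**A tempting stronger reading concerns multiplicity.** Because Sidak changes nothing when m = 1, a reader might infer that the plan fails an error-control promise across its many outcomes. The text promises adjustment within models and claims no family-wise rate across outcomes. A redundant Sidak step leaves p-values unchanged and biases nothing, and one primary outcome is named.

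**Conclusion.** The concern holds for the bootstrap rule. If the switch is made, nominal 95% BCa intervals will cover less than 95% under either resampling unit: about 82–93% (normal) or 74–86% (log-normal) with participants resampled, and 83–86% with offices resampled, which means a real two-sided error rate of about 14% to 17%. An office-level t interval covers 94–96% in the same settings. These sizes rest on four offices per arm, five people per office, ICC 0 to 0.20 and a difference in means under a true null. At ICC near zero with normal errors and participants resampled, the shortfall is only about two points.

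The trigger is poorly aimed in any case, because it tests variables rather than residuals and moves all outcomes together.

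Sidak is a minor note. It adjusts nothing in the listed models and should not be presented as multiplicity control, but this is not a failure of any stated error control.

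**What to change.** 1. Remove the rule that moves all outcomes to BCa intervals, and the description of those limits as unbiased.
2. Report 95% intervals from the mixed model with the office random effect and Satterthwaite or Kenward-Roger degrees of freedom, or t intervals on office-level summaries. State in advance which of the two is used.
3. Check model residuals outcome by outcome, and transform skewed outcomes where needed. A problem in one outcome should not change the analysis of another.
4. Minor: delete the Sidak sentence, or say that it has no effect with two-level factors, and label secondary outcomes as exploratory.

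**Cost:** analysis wording only, with no change to design or data collection. Intervals become wider. With normal errors, an office-level t interval is about 2.447/1.697 = 1.44 times the width of an office-resampled bootstrap interval. That extra width is the uncertainty that eight offices leave.
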